### Data Collection

#### Overview

A variety of data collection methods will be used, including surveys, objective assessments, checklists, qualitative interviews, site audits, website analytics, meeting minutes, and project tracking. Data collection will take place at multiple levels including the organization, provider site, coach, and client. Both online and in-person measurements will take place. Survey data specific to the trial will be collected via Qualtrics for the data from the organization and site leads and via REDCap (version 15.0.7) for the SSBC coach information and SSBC coach training, client EOI and screening, and client data. Broader site-level data (eg, memberships) will be extracted from the organizational databases. Interviews will be audio-recorded and transcribed. Meeting minutes will be taken and reviewed; website analytics (from the 3C training platform and from the SSBC website coach forums) will be downloaded and reviewed. Further details are provided below.

#### Organizational- and Site-Level Data Collection

The organizational- and site-level leads will provide or have provided informed consent for the action-research process of data collection throughout the project (ethics approval from The University of Queensland HREC #HE001455). Data collected at both the organizational and site level will include information on contextual factors, organizational readiness, acceptability, appropriateness, feasibility, and sustainability. Data will be collected via surveys, interviews, meeting minutes, site visits, and document reviews of operating protocols to understand how the program is working within the site workflow (Table 3).

**Table 3 table3:** Data collection time points for organization leads and site-level leads.

Data collection			Preimplementation		Postimplementation								
					≈3 months		1 year		2 years		3 years		4 years
**Survey**													
	Demographics and work characteristics^a^	✓											
	Organizational readiness for change	✓						✓				✓	
	Barriers and facilitators to implementation	✓						✓				✓	
	Program perceptions	✓		✓		✓		✓		✓		✓	
	Sustainability assessment					✓		✓		✓		✓	
Preimplementation adaptation workshop			✓										
Interviews			✓		✓		✓		✓		✓		✓
Document review of site operating protocol			✓		✓		✓		✓		✓		✓
Site visit and audit			✓		✓		✓		✓		✓		✓
Sustainability adaptation workshop									✓				✓
Meeting minutes			✓		✓		✓		✓		✓		✓
Membership conversions					✓		✓		✓		✓		✓
Access and input to community of practice					✓		✓		✓		✓		✓

^a^If organization or site-level leads change, then the new leads will complete demographics and work characteristics questions.

#### SSBC Australia Coach-Level Data Collection

Data collected from coaches will include information on their demographic and work characteristics, their experiences with the training, their perceptions of the program, and their fidelity to program delivery, with data collected via surveys, website analytics, and interviews. Data collection for general coaches will continue up to 4 years (Table 4); data collection for the student coaches will continue up to 12 months (Table 5). Data will be collected on the coach community of practice and the session checklists throughout program delivery.

**Table 4 table4:** Data collection time points for general health coaches.

		Profile or pretraining	End training	≈2-month post	12-month post	2 years	3 years	4 years
**Surveys**								
	Demographics	✓						
	Referral pathway							
	Training and experience	✓						
	Work and study	✓			✓	✓	✓	✓
	Training motivation							
	Confidence and knowledge	✓	✓	✓	✓			
	Knowledge check		✓					
	Feedback on the training		✓					
	Perceptions of program		✓	✓	✓	✓	✓	✓
Competency assessment			✓					
3C website analytics			✓					
Interviews				✓	✓	✓	✓	✓

**Table 5 table5:** Data collection time points for student health coaches.

			Profile or pretraining		End training		End placement^a^		1-month post placement^a^		12 months
**Surveys**											
	Demographics	✓									
	Work and study	✓									
	Student study profile	✓									
	Confidence and knowledge	✓		✓		✓		✓		✓	
	Knowledge check			✓							
	Feedback on the training			✓							
	Student placement impact					✓					
	Student training impact					✓		✓		✓	
	Perceptions of program			✓		✓		✓		✓	
Competency assessment					✓						
3C website analytics					✓						
Interview							✓				

^a^Placement duration varies from 5 to 20+ weeks depending on the program requirements.

#### Client-Level Data Collection

Data from clients will be collected via online surveys as part of the eligibility, screening, and consent process and as part of their profile, preprogram, end-of-program, and at 3, 6, and 12 months post program following consent (Table 6). In-person measurements will occur at the preprogram, end-of-program, and 12-month time points. A subsample of clients will also be invited to take part in interviews at the end-of-program and at 12 months post program.

**Table 6 table6:** Data collection time points for clients.

Client-level measure			Profile		Preprogram		End-of-program		3 months post program		6 months post program		12 months post program
			Enrollment		≈Session 1		≈Session 6		≈Time after session 6				
**Surveys**													
	EOI^a^ and screening	✓											
	Demographics	✓											
	Work and study	✓											
	Emergency contact	✓											
	Mailing list	✓											
	Connections and access			✓								✓	
	Adult Pre-Exercise Screening System			✓									
	Movement behaviors			✓		✓		✓		✓		✓	
	Dietary behaviors			✓		✓		✓		✓		✓	
	Program behaviors			✓		✓		✓		✓		✓	
	Confidence and supports			✓		✓		✓		✓		✓	
	Health-related QoL^b^			✓		✓				✓		✓	
	Loneliness			✓		✓				✓		✓	
	Health care use			✓								✓	
	Program feedback					✓							
	Program acceptability					✓							
	Prediabetes and diabetes status					✓		✓		✓		✓	
	Involvement in fitness and community			✓		✓		✓		✓		✓	
	Adverse events					✓		✓		✓		✓	
	Referral			✓		✓		✓		✓		✓	
In-person clinical measures					✓		✓						✓
Interviews^c^							✓						✓

^a^EOI: expression of interest.

^b^QoL: quality of life.

^c^Interviews in the subset only. Only those who are eligible and consent go on to be scheduled to receive the program.

### Measures and Outcomes

The measures and outcomes are mapped to the PRISM and RE-AIM framework [40], with information ordered by context, adoption and reach, implementation, effectiveness, and maintenance.

#### Context

Context will be captured under the 4 PRISM dimensions: characteristics of the implementation settings or delivery providers, perspectives on the intervention, the external environment, and implementation and sustainability infrastructure.

#### Characteristics of Implementation Settings and Delivery Providers

Characteristics captured will include the location of the delivery site, which will then be mapped to the Modified Monash Model [59] and Index of Relative Socio-Economic Advantage and Disadvantage [60] to understand remoteness and socioeconomic status of the areas in which the program is being provided; the number and type (eg, staff qualifications) of staff; the services offered (eg, group classes and types of classes); and the client base (number of members and types of memberships). Data will be collected via the site audit and reviewed annually.

Other characteristics will be collected via a CFIR-informed audit and interview. This will include, for example, understanding of other programs delivered by the site (especially those catering to a similar client base), alignment with the priorities of the site and organization, resource availability (including facilities), and existing communication channels to their members and the community.

#### Perspectives on the Intervention

Readiness for change will be assessed via the Organizational Readiness for Implementing Change tool [61] administered to both organizational- and site-level leads at preimplementation, 3 months post implementation, and then yearly. The measure consists of 12 items, each measured on a 5-point Likert scale (1=disagree and 5=agree). The Organizational Readiness for Implementing Change has demonstrated good content adequacy and reliability [61].

The pragmatic context assessment tool will be used to understand contextual barriers to change from the perspective of site leads [62]. This questionnaire, which maps to the CFIR [37], is designed to help facilitate identification of barriers and facilitators prior to implementing change [62]. It consists of 14 statements with participants asked to indicate whether they disagree (barrier), are neutral, or agree (facilitator) with each statement, and then indicate the likely effect (weak or no effect or strong effect) of this barrier or facilitator on their ability to implement the improvement. This information can then be used to map to recommended implementation strategies [62]. The pragmatic context assessment tool will be measured at preimplementation and then at 2 and 4 years to understand contextual barriers or facilitators to sustainability. Interviews, site visits, document reviews, and meeting minutes will be used to complement the survey data.

#### External Environment

Information on a range of external factors will be collected including links with community health partners, links to other support services in the area, and relevant policies and market forces. Data will be collected via interviews and audits with site leads at preimplementation and through the adaptation workshop, then annually.

#### Implementation and Sustainability Infrastructure

Information on the support provided such as ongoing training and feedback by the dedicated implementation team via communities of practice will be collected via meeting minutes (Australia) as well as analytics data from the coach forum section of the Canadian SSBC website (Canada). Each site will have its own program operating protocol (including recruitment, enrollment, evaluation, reporting, communication, and retention protocols) with this site operating protocol developed in partnership with the site, then reviewed at approximately 2 months after implementation, then annually with protocol modifications tracked. Information regarding sustainability planning will be collected via interviews with site and organizational leads at preimplementation, then annually, as well as through the sustainability adaptation workshops at 2 and 4 years.

#### Adoption and Reach

Adoption and reach measures are reported in Table 7, with data collected via a mix of surveys, interviews, and project tracking.

**Table 7 table7:** Adoption and reach outcome measures.

Outcome		Measure	Instrument
**Adoption (organization, site, and coach)**			
	Reasons for taking up program	Organizational reasons Site reasons Coach reasons^a^	Preimplementation interview Preimplementation interview Coach profile
	Uptake of health coaches	Number of coaches interested (n) Number of coaches eligible or ineligible (n) Number of coaches SSBC^b^ Australia certified (n)	Coach consent Project tracking Competency check
	Referral pathways coach^a^	How they heard about the program	Coach profile
	Characteristics of coaches	Demographic characteristics Work and experience characteristics Study profile^c^	Coach demographics Coach work and experience Student coach study profile
	Withdrawals or reasons for withdrawals	Number of withdrawals (n: site and coach) Reasons for withdrawal site Reason for withdrawal coach	Project tracking Withdrawal survey or interview Withdrawal survey or interview
	Adverse events	External factors impacting on adoption (site renewal, natural disasters, and person-made disasters)	Project tracking
**Reach (participants)**			
	Uptake of participants	Number interested (n) Number eligible or ineligible (n) Number consented (n) Number enrolled (n)	EOI^d^ and screening EOI and screening Participant consent Number onboarded to REDCap^e^ client database
	Referral pathways	How heard about the program	EOI and screening
	Characteristics of enrolled participants	AUSDRISK^f^ score, site, comorbid health conditions Demographic, work, and study	EOI and screening Demographics, suitability for exercise, work, and study
	Characteristics of ineligible participants	Demographics, AUSDRISK score (if available)	EOI and screening
	Withdrawals	Number of withdrawals (n) Reasons for withdrawals	Participant tracking Withdrawal survey

^a^Not asked for the student coaches at Logan Healthy Living, as undertaking the training is a requirement of their placement.

^b^SSBC: Small Steps for Big Changes.

^c^Asked of students only.

^d^EOI: expression of interest.

^e^REDCap: Research Electronic Data Capture.

^f^AUSDRISK: Australian Type 2 Diabetes Risk Assessment Tool.

#### Demographic Characteristics (All Participants)

Characteristics to be measured on all participants (organizational lead, site leads, health coaches, and clients) include age (year of birth), sex assigned at birth, gender, location (provider site), ethnic origins, country of birth (Australia or other), main language spoken at home (English or other), disability status, highest education level, home postcode, and paid employment and study status.

#### Work History and Experience (Health Coaches)

All health coaches will additionally be asked about their qualifications, time worked in the health or health promotion field, completion of any courses in behavior or behavior change, amount of training in health or health promotion, cultural safety, MI (5-point scale from 1=none to 5=extensive), reasons for doing this training, and experience in using MI and working with clients with type 2 diabetes or prediabetes (5-point scale from 1=none to 5=extensive).

#### Student Study Profile (Student Health Coaches)

Student health coaches will be asked additional questions to the general health coaches that are specific to their university training, namely, student status (domestic or international), university, program of study, degree level (undergraduate or postgraduate), year of study, and number of full-time placements completed (0 to 5+).

#### Suitability for Exercise (Clients)

Clients will be asked to complete the Adult Pre-Exercise Screening System [63] before the intervention. None of the survey responses are automatic disqualifications for participation. Responses will be used by coaches to discuss any relevant safety concerns about participation with participants at their first session, including escalating to a review by an appropriate allied health professional or medical practitioner as required, based on the site-level protocols. This questionnaire also provides open text for the client to record anything else they would like to talk about with their coach or like their coach to be aware of.

#### Contextual Measures (Clients)

Clients will be asked about their social connections and access to healthy food, transport, recreation spaces, assistance with legal matters, housing or accommodation, and health services using the 6-item access subscale and the single item on connections outside of family (on a 9-point scale from 0=not at all connected or poor access to 8=very connected or easy access) from the Steps to Better Health Questionnaire [64]. Clients will also be asked about their involvement in activities outside the home (social, exercise groups, art and craft, and performing arts), their membership with any fitness facilities (the study site and other), and their referral of others to the SSBC Australia program and to the site.

#### Other

All coaches are asked to indicate their level of motivation to do the required training to become a SSBC Australia coach (0=not at all to 10=extremely). Further, health coaches who are not students will be asked their reasons for becoming a coach (open text) and how they heard about the program. This will not be asked of the student coaches, as they will all do the training as part of their placement requirements. Referral pathways will also be captured as part of the screening and consent process for clients.

#### Implementation

The implementation outcomes will consider both the SSBC Australia coach training and program delivery. SSBC Australia will be considered practicable on the APEASE criteria if it is able to be appropriately implemented (high fidelity) for both these elements.

#### Implementation—Health Coach Training

Fidelity of the training process will be considered in terms of the number of core training components completed: the 7 online Canadian modules (assessed via website analytics), the 4 core Australian-specific modules and review of the client workbook (assessed via self-reported completion), the knowledge check quiz, and the competency assessments. All components are expected to be completed for training fidelity.

Acceptability, appropriateness, and feasibility of the training will be measured following completion of the competency check process via a bespoke survey. In total, 5 items ask about the acceptability, usefulness, appropriateness, feasibility, and value (to current and future career) with responses on a 5-point Likert scale (1=not at all to 5=extremely), and 2 items will be asked on satisfaction regarding the length and content of the training in general (1=extremely dissatisfied to 5=extremely satisfied). For each of the training components the coach indicated they did, they will be asked how useful the component was (1=not at all useful to 5=extremely useful). One question will be open text for any other feedback. The self-reported time spent on each of the training components will be captured, along with details about training for their competency checks (since the sites have flexibility in how these are conducted).

#### Implementation—Program

### Provider Level (Coach, Site Lead, and Organization Lead)

Acceptability, appropriateness, and feasibility of the program from the perspective of coaches, site leads, and organization leads will be measured by the Acceptability of Intervention Measure, the Intervention Appropriateness Measure, and the Feasibility of Intervention Measure [65]. These measures, which can be used separately or together, have demonstrated high test-retest reliability (*R*=0.73 to 0.88) and good structural validity [65]. All measures use the same 5-point Likert scale (1=completely disagree and 5=completely agree), and each measure has 4 items. Scores for the items within each domain are averaged, with higher scores indicating higher acceptability or appropriateness or feasibility. Data will be collected at preimplementation, approximately 2-3 months after implementation (to capture short-term impressions), and then yearly until year 4. Student coaches will complete the measures at preimplementation, end-of-placement, and 1 month and 12 months after implementation. These factors will also be explored via interview and open-text questions approximately 2-3 months after training, then yearly until year 4 for the general coaches and site and organizational leads and at the end-of-placement for the student coaches.

Fidelity of program delivery (site level) will be considered in terms of adherence to the site operating protocols, assessed during quarterly project site meetings.

Fidelity of coaching delivery (coaches) will be considered in terms of adherence to the SSBC Australia coaching session checklist. This checklist, which is embedded into each of the 6 coaching sessions, will capture whether the core education components for each session were covered.

Quality of the coaching (coaches) will be self-rated by the health coaches at the end of each session via a checklist. Items include client engagement with the session (single item, 1=none to 6=excellent) and overall quality of the sessions as defined by the fidelity checklist (single item, 1=none to 6=excellent). A random sample of sessions will be recorded (with permission from the client), and coaches will be asked to rate their use of MI skills (5 items, all 1=strongly disagree to 5=strongly agree). These sessions will be reviewed by the research team against these same criteria (engagement, quality, and the use of MI skills). These recordings will also be used to confirm fidelity indicators.

The number and type of adaptations to the coach training and to program delivery made prior to and then during delivery will be tracked via the research team. The number and type of adaptations made in order to sustain SSBC in the Australian context (should sites decide to continue delivery) will be recorded as part of the sustainability adaptation workshop.

Sustainability of program delivery (site level) will be determined by the decision of the delivery site to continue delivery of the program at 2 years (end of research-funded support) and 4 years (end of evaluation support). Reasons for the decision will be captured as part of the yearly interviews with site and organization leads.

Costs will be considered in terms of time for coach training, program delivery and evaluation, site lead time, administration time, and provision of the in-kind membership. Coach training time will be asked of coaches as part of their posttraining survey suite. Each of the 6 client sessions will be time-stamped (start and finish) to track program delivery and evaluation time. Site lead time will be determined from their scheduled time allocated to the project (minus any training or program delivery time). Estimation of administration time will be asked at the regular site meetings and recorded by the research team.

### Client Level

Program acceptability from a client perspective will be asked via survey at the end of the program using the Acceptability of Intervention Measure and Intervention Appropriateness Measure [65]. Clients will also be asked 4 open-ended questions on barriers experienced as part of the program, how they think the program can improve, what they liked about the program, and any other feedback relating to their experience. A subset of participants, randomly selected, will be asked to take part in an interview to gain further insights on their experience, with interviews conducted at the end of the program and at 12 months (anticipated n=10-15 at each time point).

Program satisfaction will be measured at the end of the program via a survey developed specifically for this evaluation. In total, 9 questions will ask about satisfaction in terms of their overall experience, their coach, the nutrition content, the physical activity content, the program workbook, the location of sessions, the length of sessions, the length of program, and their experience with administration (scheduling), with response options on a 7-point Likert scale (1=extremely dissatisfied and 7=extremely satisfied). Clients will also be asked to indicate on a scale of 0=not likely at all to 10=definitely their likelihood of promoting the SSBC Australia program to family, friends, or colleagues.

Fidelity of program receipt will be considered in terms of the extent to which the program was received by the client as intended. It will be measured by the number of coaching and exercise sessions successfully completed by the client (a maximum 12: 6 coaching and 6 exercise) and will be tracked by the health coach as part of their session checklist.

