### Ethical Considerations

The study has received ethics approval from The University of Queensland Human Research Committee for the adaptation to the Australian context (#HE001455, #HE000500, and #HE001547), understanding of context and barriers and enablers to implementation from a site and provider perspective (#HE001455), and program delivery and evaluation (#HE001123 and #HE001280). All participants are provided with an electronic participant information and consent sheet prior to participation, where it is emphasized that participation in the research is voluntary. Participants can withdraw at any time without consequence; however, data collected up to that point may be used in analyses. Data are identifiable when collected and deidentified for analyses. Client participants are provided with up to 6 weeks of membership at their SSBC Australia site (with this paid for by the delivery site) and provided the program for free. Sites are provided with funding from the grant to deliver the program for the first 2 years.

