### Aims of the SSBC Australia Trial

The overall aim of the trial is to evaluate the contextually adapted version of the Canadian-developed SSBC program (SSBC Australia). Specifically, we aim to evaluate the uptake (adoption) by coaches; reach of the program; program implementation, including program acceptability (at the provider site, coach, and client level) and contextual factors influencing implementation; program effectiveness; and sustainability of the program, including delivery costs and ongoing delivery.

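### Client acceptability and satisfaction ratings are scheduled only in the end-of-program survey, and no rating is listed for clients who withdraw, so the scores are plausibly biased upward

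*Protocol article*

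**What the plan says.** The Aims section of the protocol article lists program implementation as something to be evaluated, "including program acceptability (at the provider site, coach, and client level"). Acceptability is also one of the APEASE criteria that guide modifications during the trial and will inform the case for expansion (Frameworks for Evaluation and Reporting; Strengths and Limitations).

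Under Client Level, the schedule for clients is explicit:

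- Acceptability and appropriateness: "Program acceptability from a client perspective will be asked via survey at the end of the program", using the Acceptability of Intervention Measure and the Intervention Appropriateness Measure.
- Satisfaction (9 items): "Program satisfaction will be measured at the end of the program via a survey developed specifically for this evaluation". A 0-10 item on likelihood of promoting the program is described with it.
- Barriers: "Clients will also be asked 4 open-ended questions on barriers experienced as part of the program", described with the acceptability survey.
- Interviews: a randomly chosen subset, "with interviews conducted at the end of the program and at 12 months (anticipated n=10-15 at each time point").

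Table 6 agrees. Its rows for program feedback and program acceptability are ticked in the end-of-program column only, which is headed as about session 6. The 3-, 6- and 12-month surveys carry neither.

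For clients who leave, the Reach part of Table 7 gives the outcome as "Number of withdrawals (n) Reasons for withdrawals" and the instruments as "Participant tracking Withdrawal survey". Ethical Considerations adds: "Participants can withdraw at any time without consequence; however, data collected up to that point may be used in analyses".

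**The concern.** A client's decision to leave is itself likely to be related to how acceptable the program was. If acceptability is rated once, at about the last session, clients who have gone by then contribute no score unless they still answer that survey. The withdrawal data listed tell us why they left, but not on a scale that can be combined with the scores of those who stayed.

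The analysis described does not offset this. Data Analysis says that implementation outcomes will be described. Adjustment for predictors of missing data and the multiple-imputation sensitivity analysis are set out for the client effectiveness and maintenance models. No earlier client rating of acceptability exists on which an imputation could draw.

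At stake is an average score, or a percentage satisfied, that looks precise and is too favorable. It would be used when adapting the program and arguing for its expansion. The bias depends on who answers, so it does not shrink with enrollment.

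**Working it through.** **1. What the plan quantifies.** The article states no precision, response rate or threshold for acceptability. The nearest figure is the 20% attrition in Target Sample Size—Participants, an allowance made for the physical activity outcome (MVPA). That calculation reproduces:

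- SD of change = 330 x sqrt(2 x (1 - 0.4)) = 361.5.
- 80% power: (361.5 x (1.960 + 0.842) / 60)^2 = 285; x 1.099 = 314 after rounding up; / 0.8 = 393.
- 90% power: (361.5 x (1.960 + 1.282) / 60)^2 = 382; x 1.099 = 420; / 0.8 = 525.
- The t-distribution version gives 395 and 528-529. The plan states 394-528.

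The sample-size statement is sound. Only its attrition figure is borrowed here, as an assumption.

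**2. Clients without a rating, if 20% carried over.** 500 x 0.20 = 100 of the 500 enrolled. At 10% or 30% (assumed) it would be 50 or 150.

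**3. Effect on a mean score.** With d the share not answering, overstatement = d x (responder mean - non-responder mean). The gaps are assumed; no document gives one.

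| Assumed gap (1-5 scale) | d = 10% | d = 20% | d = 30% |
|---|---|---|---|
| 0.5 | 0.05 | 0.10 | 0.15 |
| 1.0 | 0.10 | 0.20 | 0.30 |
| 2.0 | 0.20 | 0.40 | 0.60 |

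**4. Comparison with sampling error.** With 400 respondents and an assumed SD of 0.6 to 1.0, the 95% half-width is 1.96 x SD / sqrt(400) = 0.06 to 0.10 points, ignoring clustering. If a gap of about half a point or more exists, the bias is at least as large as the interval the report would show. The comparison does not show that such a gap exists.

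**5. Effect on a percentage.** If 90% of responders find the program acceptable (assumed), the figure for all enrolled at d = 20% is 0.8 x 90% + 0.2 x q:

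- q = 70%: 86%
- q = 50%: 82%
- q = 30%: 78%
- q = 0%: 72%

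**The case against.** The strongest reply has four parts.

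**The withdrawal survey's items are not shown.** Table 7 maps outcomes to instruments; it is not a questionnaire, and a condensed article would not normally print one. This stands: the survey may already hold such items. What remains is that reasons for leaving are the only content the article names for it.

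**The survey is not confined to finishers.** A reader might infer that acceptability will be judged only on people whom the program suited. The documents do not support that. No text limits the end-of-program survey to clients who completed all sessions, and dissatisfied clients who stay can answer. The random interview subset is not limited to finishers either.

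**There is other evidence.** Reasons for withdrawal are themselves information on barriers. Sessions completed out of 12 and coach-rated engagement after each session cover clients who later leave. There are interviews at 12 months, and coaches, site leads and organization leads also rate acceptability. All of this stands as partial evidence. None of it is a client rating comparable with the end-of-program scores. The interviews are few and are not stated to include clients who withdrew.

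**The size is assumed and the outcome is descriptive.** This stands too. The 20% is an MVPA attrition allowance, not a withdrawal rate, and may include people who simply do not return a survey. People also leave for reasons unrelated to the program. A reader might also infer that the APEASE verdict on acceptability will be wrong. The article gives a rule for affordable and one for practicable but none for acceptable, so there is no pass or fail result to overturn.

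**Conclusion.** The point holds in a limited form. Client ratings of acceptability, appropriateness and satisfaction will come only from those who answer at about session 6, no comparable rating is listed for clients who withdraw, and the stated analysis does nothing to offset selective non-response. An upward bias is plausible but not demonstrated. Its illustrative size is 0.1 to 0.4 points on the 1-5 scale. That rests on two assumptions: that the 20% MVPA attrition carries over, and that non-responders would score 0.5 to 2.0 points lower. With no gap there is no bias.

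This is a minor matter. It concerns a named aim that is reported descriptively, and neither primary outcome (MVPA change and delivery fidelity) is affected. It is worth raising because the remedy costs little and the ratings cannot easily be recovered once clients have left.

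**What to change.** 1. Unless they are already there, add the acceptability and appropriateness items, the overall satisfaction item and the barriers question to the existing withdrawal survey. Mark them as optional, since withdrawal is to be without consequence. If the survey already includes them, say so in Table 7.
2. Send the end-of-program survey to clients who stop attending without formally withdrawing, at the time their course would have ended.
3. Report client acceptability overall and separately for completers and non-completers, beside the numbers who withdrew and who did not respond.

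The cost is a few existing questions on a survey already planned, one more scheduled send, and two extra rows in a descriptive table. The drawback is that leavers may respond at a low rate. Their scores would then be only indicative, and the response rate must be reported with them.
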